### Neuroimaging data analysis

#### Primary and exploratory imaging outcomes

The following two measures are specified as the primary imaging outcomes: (1) functional connectivity (FC) of resting-state fMRI; and (2) prefrontal regions of interest (ROI) activation during the VFT as measured by fNIRS. These primary endpoints are considered confirmatory, with hypothesis testing guided by FDR correction as described below. All other imaging metrics described in this section are considered exploratory, and any observed associations will be interpreted as hypothesis-generating, requiring validation in future studies.

All neuroimaging data will be processed and analyzed using SPM12 (Wellcome Centre for Human Neuroimaging, London, UK), Homer2, and the NIRS-SPM toolbox in the MATLAB R2018a environment. To evaluate potential attrition bias, we will compare baseline demographic and clinical characteristics between participants who complete imaging assessments and those who do not. Furthermore, where feasible, we will consider using mixed-effects models to reduce bias associated with missing data. We will report reasons for missing imaging data.

#### fMRI data processing and analysis

BOLD-fMRI data preprocessing steps will include: slice timing, realignment, normalization, detrending, and bandpass filtering (0.01–0.08 Hz). Subsequently, the following brain functional indicators will be calculated: FC—the primary fMRI outcome—will be analyzed to assess network-level changes, while exploratory indicators will include amplitude of low-frequency fluctuation (ALFF), fractional ALFF (fALFF), regional homogeneity (ReHo), and functional connectivity strength (FCS). In addition, 3D-T1 structural images will be analyzed using SPM12 with the CAT12 toolbox for voxel-based morphometry (VBM) to extract structural metrics such as gray matter volume and cortical thickness. DTI data will be preprocessed using FSL 4.1.9 software, including head motion correction, eddy current correction, and tensor model fitting, to obtain fractional anisotropy (FA) and mean diffusivity (MD) maps.

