### Imaging data acquisition

#### MRI data acquisition

All MRI examinations will be performed at the MRI Center of West China Hospital, Sichuan University, on a 3.0 T scanner (Discovery MR750; GE Healthcare, Milwaukee, USA) equipped with an eight-channel phased-array head coil. Before scanning, each participant will be screened for contraindications and asked to remove all metallic items. Foam cushions will be placed around the head to minimise motion, and earplugs will be provided to attenuate acoustic noise. Scans will be acquired with the participant lying supine and remaining alert throughout.

A high-resolution structural dataset will be obtained with a three-dimensional T1-weighted spoiled gradient-echo sequence: repetition time/echo time (TR/TE) = 6.2/2.5 ms, field of view = 256 × 256 mm^2^, matrix = 256 × 256, voxel size = 1.0 × 1.0 × 1.0 mm^3^. BOLD images will be acquired using a gradient echo planar imaging (GRE-EPI) sequence: TR/TE = 2000/30 ms, flip angle = 90 degrees, slice thickness = 2 mm, field of view (FOV) = 128 × 128 mm^2^, voxel size = 2 × 2 × 2 mm^3^. DTI sequences will be acquired FOV = 256 × 256 mm^2^, TR = 6,500 ms, matrix = 128 × 128, number of diffusion-encoding directions = 32, slice thickness 2 mm, layer spacing = 0, and gradient values b = 0 s/mm^2^ and b = 1,000 s/mm^2^.

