### Objectivity in outcome assessment and quality control

All clinical outcomes will be assessed by trained evaluators who are blinded to group allocation and not involved in treatment delivery. Assessors will follow a standardized assessment manual to minimize inter-rater variability, and role separation will be maintained between intervention operators, outcome assessors, and statisticians. Data will be recorded on case report forms and verified by independent checking to reduce entry errors, and protocol deviations as well as concomitant rehabilitation potentially affecting cognition will be documented. For neuroimaging, preprocessing and metric extraction will follow a pre-specified pipeline, with imaging analysts blinded to group allocation. Quality control will include motion/artifact inspection and predefined exclusion criteria.

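### The BOLD data are band-pass filtered before the exploratory metric fALFF is calculated, which strips out most of its denominator and inflates and distorts it

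*Protocol article*

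**What the plan says.** Under fMRI data processing and analysis, the protocol article lists the BOLD preprocessing steps and links them to the metrics in this order: "slice timing, realignment, normalization, detrending, and bandpass filtering (0.01–0.08 Hz). Subsequently, the following brain functional indicators will be calculated". FC comes first, as the primary fMRI outcome. Then "exploratory indicators will include amplitude of low-frequency fluctuation (ALFF), fractional ALFF (fALFF), regional homogeneity (ReHo), and functional connectivity strength (FCS". A single processed series appears to feed all of these metrics, and no section gives fALFF a separate unfiltered branch.

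Under MRI data acquisition, the BOLD sequence has "TR/TE = 2000/30 ms, flip angle = 90 degrees", which sets the range of frequencies that can be measured.

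Under Primary and exploratory imaging outcomes, FC and fNIRS prefrontal activation are the two primary imaging outcomes, and "All other imaging metrics described in this section are considered exploratory".

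Under Objectivity in outcome assessment and quality control, "preprocessing and metric extraction will follow a pre-specified pipeline".

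The article does not state the filter type, the frequency band used for fALFF, or the number of BOLD volumes.

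**The concern.** fALFF is a ratio. Its numerator is the amplitude in the low-frequency band, and its denominator is the amplitude over the whole measurable range. It is informative only because voxels differ in how much amplitude lies outside the low-frequency band. A band-pass filter is designed to remove exactly that amplitude. If it is applied first, the numerator is left nearly intact while the denominator shrinks towards it.

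An analyst who follows the written order would therefore report, under the name fALFF, a number that is not fALFF. The statistical section plans correlations of clinical scales with imaging parameters in general, and exploratory imaging associations are meant to generate hypotheses. A hypothesis drawn from a distorted ratio would be a poor guide to later work. A null result on an index squeezed towards its ceiling would say little.

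**Working it through.** The document gives no fALFF value, so there is no stated figure to reproduce. The check is of the order of operations.

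**Inputs from the document**
- Pass band 0.01–0.08 Hz, applied before the metrics (fMRI data processing and analysis).
- TR = 2000 ms = 2 s (MRI data acquisition).

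**Assumed, because not stated**
- The usual definition: fALFF = Σ A(f) over the low-frequency band ÷ Σ A(f) over the full range to Nyquist, where A(f) is spectral amplitude.
- Numerator band 0.01–0.08 Hz, unless noted otherwise.
- 180, 240 or 300 volumes.

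**Step 1: measurable range.** Nyquist = 1 / (2 × 2 s) = 0.25 Hz.

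**Step 2: what the filter removes.** The pass band is 0.08 − 0.01 = 0.07 Hz wide, and 0.07 / 0.25 = 0.28. For a flat spectrum, unfiltered fALFF would be about 0.28, and the other 72% of the denominator lies outside the pass band. With 240 volumes, 34 of 120 frequency bins fall in the band: 34 / 120 = 0.283.

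**Step 3: the ratio after filtering.** With filter gain H(f), the index becomes Σ H·A over the band ÷ Σ H·A over the full range. If H = 1 inside the band and 0 outside it, the two sums are identical and the ratio is 1 for any spectrum. If H falls off gradually, the denominator keeps some leaked amplitude and the ratio lies between the unfiltered value and 1.

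**Step 4: simulation.** 5,000 voxels per run, with coloured plus white noise varying by voxel. Ranges are across 180, 240 and 300 volumes and, for the Butterworth row, design orders 2 and 4.

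| Input series | Mean fALFF | Between-voxel SD | Correlation with unfiltered fALFF |
|---|---|---|---|
| Unfiltered | 0.32–0.33 | 0.033–0.038 | – |
| Ideal filter, same band | 1.000 | about 2 × 10⁻¹⁶ | none (constant) |
| Zero-phase Butterworth | 0.79–0.87 | 0.035–0.047 | 0.31–0.49 |
| Ideal filter, narrower numerator (0.01–0.027 Hz, assumed) | 0.28–0.30 | 0.05–0.06 | not calculated |

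Individual Butterworth values ran from 0.62 to 0.96. In the last row the index is not constant, but it is a share within the pass band, because everything outside 0.01–0.08 Hz has gone from the denominator.

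**Step 5: sensitivity to the assumptions.** With first-order autoregressive noise (coefficients 0–0.9, 240 volumes), unfiltered fALFF had median 0.40 (2.5th to 97.5th percentile 0.27–0.53) and was 1.00 throughout after an ideal filter. A further simulation with zero-phase Butterworth filters gave means of about 0.72–0.87 and correlations with true fALFF of about 0.43–0.83. Over all runs, gradual-edge filtering put the mean at about 0.7–0.9 against 0.3–0.4 unfiltered, and the correlation with the intended metric anywhere from 0.31 to 0.83.

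**Step 6: the other metrics.** ALFF uses only in-band amplitude. In the simulation it was the same before and after an ideal filter (relative difference below 10⁻¹⁵). FC, FCS and ReHo have no out-of-band denominator, so this problem does not arise for them.

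**The case against.** The strongest reply is that this is a condensed article. Preprocessing takes one sentence and the metrics another. The adverb joining them may only introduce the next stage, without naming the input series for each metric. Branching by metric is the kind of detail that a full imaging procedure would hold. The quality-control section promises a pre-specified pipeline but does not say that this paragraph is the whole of it. This has some force: the imaging team may well intend an unfiltered branch. But the article does more than leave the detail out. It states an order and puts fALFF in the list that comes after filtering, and nothing elsewhere corrects that.

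The second reply concerns size. A reader might infer that fALFF would equal 1 everywhere and carry no information, that any significant cluster would be an artefact, or that a null result would be taken as no regional effect of PC6 stimulation. The document does not support these readings. A constant value of 1 needs both an ideal filter and a numerator band equal to the pass band, and neither is stated. With gradual-edge filters the values spread and keep a weak to fairly strong relation to true fALFF. The article does not say that fALFF will be tested voxel by voxel. ALFF and ReHo, which are also regional measures, remain available.

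The third reply is that the metric is exploratory and will be read with caution. That limits the importance of the point. It does not excuse calculating a different quantity under the metric's name, since caution in interpretation cannot recover the lost denominator.

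**Conclusion.** The point holds in a limited form. As ordered in the article, fALFF is calculated from data that have lost most of the amplitude its denominator needs. Under an ideal filter over the same band it is degenerate; under a gradual-edge filter it is inflated to roughly twice its unfiltered level or more, and its variation depends partly on the filter. None of the filter and band combinations tried recovers the intended metric.

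The direction follows from the definition and the stated order alone. The sizes depend on the assumed noise structure, filter type, fALFF band and number of volumes. The consequence is confined to one exploratory, hypothesis-generating metric. The MoCA primary outcome, FC and fNIRS prefrontal activation as primary imaging outcomes, ReHo and FCS are untouched, and ALFF is unchanged under an ideal filter. It should be corrected because the written rule is wrong for this metric and the repair costs almost nothing; no main conclusion of the trial depends on it.

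**What to change.** In fMRI data processing and analysis, add one sentence: fALFF is calculated from the detrended series before band-pass filtering, as the 0.01–0.08 Hz amplitude divided by the amplitude over the full range to 0.25 Hz. Keep the filtered series for FC, FCS and ReHo. ALFF may come from either series, provided the choice is stated. If the detailed imaging procedure already has this branch, the article's wording only needs to match it. No new data, scans or analyses are required.

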#### fNIRS data processing and analysis

After format conversion, fNIRS raw data will undergo channel quality assessment, motion artifact correction (Wavelet-MDL), bandpass filtering, optical density change calculation, and HbO/HbR concentration extraction. The task paradigm will be a VFT, and a generalized linear model (GLM) will be constructed using an event-related design to extract the *β* value for each channel. Based on channel layout, ROIs such as the frontal lobe and motor areas will be defined. Activation within the prefrontal ROI during VFT—the primary fNIRS outcome—will be extracted as average activation intensities for statistical comparisons, including between-group and within-time point comparisons using ANOVA or nonparametric tests as appropriate. Repeated measures analysis of variance will be used to test Group × Time interaction effects. Exploratory analyses may include calculation of functional connectivity matrices to assess brain network integration and local clustering characteristics.

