#### fNIRS data acquisition

This study will employ fNIRS to repeatedly acquire patients’ brain functional activity at three time points (before the first treatment, after the first treatment, and after the last treatment). Data will be collected using an fNIRS system (NIRSCAN, Huichuang, China) with wavelengths of 740 nm and 850 nm, consisting of 48 effective channels (22 light source probes and 16 detector probes). Cortical hemodynamic changes will be sampled at 11 Hz, with 3 cm inter-channel spacing covering the frontal and parietal lobes.

During data acquisition, the assessment room will be kept quiet, with only the patient and examiner present. The patient will be seated upright with head immobilized, and the probe array will be secured to the scalp. After probe adjustment and verification of optimal signal quality across all channels, data collection will began. The Verbal Fluency Test (VFT) (41) will be used as the cognitive activation task. As a validated measure of executive function, VFT reflects complex cognitive processes and has been extensively used in fNIRS research (42). Each trial will comprise a 60-s pre-task baseline, a 60-s task period (divided into three 20-s blocks), and a 60-s post-task recovery period. During the task, participants will generate as many words as possible based on three randomly presented Chinese characters (e.g., ‘Jiang’, ‘Ri’, ‘Da’), with the number of valid words recorded as a measure of cognitive performance.

Based on potential factors such as patient intolerance to imaging procedures, imaging data quality issues, or other possible interfering factors, we anticipate an imaging attrition rate of approximately 10%.

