Moreover, we specifically applied multimodal imaging techniques for objective efficacy evaluation. fNIRS data will be collected at three time points (baseline, immediately after the first session, and after the 15th session) to capture both acute and cumulative effects. The post-first-session scan detects rapid hemodynamic changes that reflect the immediate neuromodulatory impact of a single magnetic- or acupuncture-stimulus, consistent with rTMS-related long-term potentiation (LTP) or inhibition mechanisms (58). This immediate measurement also serves as an early indicator of whether the target brain regions respond to the intervention. The time point after 15 sessions evaluates the cumulative or sustained effects following the full course of treatment. Both neuromodulation and acupuncture may exhibit dose-dependent plasticity effects, where repeated stimulation over days or weeks leads to lasting reorganization of neural circuits and improvements in clinical outcomes (59, 60). Therefore, data collected at the end of the 15-session course can reveal long-term therapeutic effects and changes in brain networks that underlie sustained cognitive improvements. Most importantly, comparing immediate and long-term changes can distinguish transient physiological responses from enduring neuroplastic adaptations. Resting-state fMRI provides whole-brain network analysis, as well as the reconstruction of cognition-related pathways (e.g., hippocampus-posterior cingulate cortex) (61–63). If magnetic stimulation at the PC6 acupoint has a unique effect, we anticipate that fMRI will capture specific network reorganization patterns in the MAG group, such as enhanced connectivity within the DMN and between the DMN and SN, which aligns with mechanisms of post-stroke cognitive recovery. Furthermore, we plan to correlate imaging metrics with cognitive scores to examine the relationship between brain network changes and clinical outcomes, thereby deepening the understanding of the underlying mechanisms.

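### The Group × Time test of the confirmatory fNIRS outcome is a complete-case repeated-measures ANOVA, while mixed models are only an option; the cost is some precision and a small possible bias in the acute contrast

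*Protocol article*

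**What the plan says.** - **Status.** The section on primary and exploratory imaging outcomes names two primary imaging measures: resting-state functional connectivity, and prefrontal activation during the verbal fluency task on fNIRS. It adds: "These primary endpoints are considered confirmatory, with hypothesis testing guided by FDR correction as described below".
- **Test.** The section on fNIRS processing and analysis first plans comparisons of prefrontal activation "including between-group and within-time point comparisons using ANOVA or nonparametric tests as appropriate". The next sentence reads: "Repeated measures analysis of variance will be used to test Group × Time interaction effects".
- **Missing imaging data.** The imaging outcomes section plans a baseline comparison of patients with and without completed imaging and a report of reasons for missing data. On method it says only that "where feasible, we will consider using mixed-effects models to reduce bias associated with missing data". Multiple imputation appears under clinical data analysis, not under imaging.
- **Schedule.** The fNIRS acquisition section has recordings "at three time points (before the first treatment, after the first treatment, and after the last treatment". The Discussion says the three recordings are there "to capture both acute and cumulative effects" and that "comparing immediate and long-term changes can distinguish transient physiological responses from enduring neuroplastic adaptations". Table 1 marks fNIRS only at baseline and week 3.
- **Expected loss.** The fNIRS acquisition section states "we anticipate an imaging attrition rate of approximately 10" per cent. It does not say at which recording the loss falls, or whether it includes the 10% trial attrition in the sample size section.

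**The concern.** Classical repeated-measures ANOVA needs a full set of recordings from each patient. The article states this test without condition, and states the method that would retain incomplete patients only as a possibility. For an outcome called confirmatory, the handling of incomplete patients is then settled after the data are in.

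Under the three-recording schedule, a patient recorded at baseline and after session 1 who misses the last scan drops out of the Group × Time test. Both values needed for the acute change were collected, and that test ignores them. If the chance of missing the last scan is related to the post-session-1 value, the completers are a selected group and their acute change is shifted. Comparing baseline characteristics describes the loss but does not correct it, and it cannot reveal selection that arises after session 1.

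**Working it through.** **1. The plan's own figure.** The article gives no sample size or power for fNIRS. Its only calculation is for MoCA: one-way ANOVA, three groups, f = 0.32, α = 0.05, power 0.80, total 99. With noncentrality N·f², power first reaches 0.80 at N = 98 (0.804). Rounded up to equal groups this is 99 (0.808), so the figure reproduces.

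**2. Patients kept by the Group × Time test.** Assume that everyone has the first two recordings and a share m misses the last. Complete triples = 105 × (1 − m); observed acute pairs discarded = 105 × m.

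| m | Complete triples | Acute pairs discarded |
|---|---|---|
| 5% | 99.8 | 5.2 |
| 10% (stated imaging attrition) | 94.5 | 10.5 |
| 15% | 89.2 | 15.8 |
| 19% (10% imaging on top of 10% trial attrition: 1 − 0.9 × 0.9) | 85.1 | 19.9 |

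The last row needs the two rates to add, which the article does not say.

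**3. Precision when loss is unrelated to response.** Take 35 per arm, unit SD and within-patient correlation 0.5. The acute change then has variance 2 × (1 − 0.5) = 1. The standard error of a two-arm difference is √(2/35) = 0.239 with all pairs and √(2/(35 × 0.9)) = 0.252 among completers. Simulation gave 0.241 and 0.253, with no bias. That is about 5% on the standard error.

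As a yardstick only, f = 0.32 in a one-way ANOVA gives power 0.833 at N = 105, 0.786 at 94 and 0.739 at 85. This is the MoCA planning effect, not an fNIRS effect. A mixed model would not recover the whole gap, because the missing last scans stay missing.

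**4. Bias when loss depends on the post-session-1 value.** Let ρ be the correlation between recordings and suppose loss occurs in one arm. The completers' acute change in that arm shifts by (1 − ρ) × (completers' mean post-session-1 value, in SD units).

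- 10% loss, logistic with slope 1: completers' mean about 0.09 SD. Shift about 0.055, 0.037 and 0.018 SD for ρ = 0.4, 0.6 and 0.8.
- Exactly the lowest 10% lost: mean 0.195 SD. At ρ = 0.8 the shift is 0.195 × 0.2 = 0.04 SD.
- Exactly the lowest 20% lost: mean 0.35 SD. At ρ = 0.4 the shift is 0.35 × 0.6 = 0.21 SD. This is the extreme case.

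In this setting the final-minus-baseline contrast among completers is essentially unbiased. With equal correlations, the baseline and final means both move by ρ times the same amount, and the difference cancels.

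**5. A different loss mechanism.** Let loss in both arms depend on the acute change itself, with a true between-arm acute difference of 0.50 SD and ρ = 0.5. Completers then give 0.46 (about 11% missing) or 0.39 (about 16% missing, stronger selection), against 0.50 from all observed pairs. Here the final-minus-baseline contrast does not cancel fully. The covariance of the final and acute changes is ρ − ρ − ρ + 1 = 1 − ρ, and the variance of the acute change is 2(1 − ρ). The final contrast therefore moves by half as much: (0.50 − 0.46)/2 = 0.02 and (0.50 − 0.39)/2 ≈ 0.05 SD.

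**6. What the mixed model does.** If only last recordings are missing and each group has its own mean at each time, the likelihood splits into the first two recordings and the last given those two. The acute contrast is then estimated from all observed pairs. The final contrast is valid when loss depends on observed recordings.

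**The case against.** The article already recognises imaging attrition, names mixed models, and plans to compare completers with non-completers. It is a condensed account, and the final missing-data model and covariance structure are commonly left to the analysis plan. That is fair for the covariance detail. It does not cover the mismatch between a test stated outright and a remedy stated only as a possibility, for an outcome labelled confirmatory.

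A reader might infer that stopping early erases a patient's acute-effect data altogether. The text does not support that. The sentence before the Group × Time test plans comparisons that can use every post-session-1 value, so the loss is confined to the Group × Time test.

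Three further objections stand. The acute contrast exists only under the three-recording schedule, and Table 1 shows two. The confirmatory label is attached to the measure, and nowhere to the acute contrast specifically. Nothing in the documents links missing scans to the fNIRS value: the reasons given are intolerance, data quality, adverse reactions, worsening, and personal or social causes. Some of these could be related to response, but that is an assumption.

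**Conclusion.** The point holds in limited form. For a confirmatory imaging outcome, the article commits to a complete-case test and leaves the better method optional. At the stated 10% attrition, if it falls at the last scan, about 94–95 of 105 patients enter the Group × Time test and 10–11 observed acute pairs are unused. The certain harm is a modest loss of precision. A bias of about 0.02–0.06 SD in the acute contrast follows only if loss in one arm depends, probabilistically, on the post-session-1 value.

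Two larger figures should not be taken as expected. A shift of 0.21 SD requires losing exactly the lowest fifth of one arm at correlation 0.4. About 85 remaining patients requires two attrition rates to add, which the text does not state. Nor do the calculations show that the end-of-treatment contrast is seriously distorted: it was essentially unbiased when loss depended on the post-session-1 value, and moved by half the acute shift when loss depended on the acute change.

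Severity is minor to moderate. This is an imaging outcome, and the MoCA analysis is unaffected.

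**What to change.** 1. In the fNIRS processing and analysis section, make a linear mixed model the stated Group × Time test for prefrontal activation. It should have group, time and group × time, unstructured covariance over the recordings, and every randomised patient with at least one recording. Name the acute (post-session-1 minus baseline) and end-of-treatment (final minus baseline) contrasts. Keep the complete-case ANOVA as a sensitivity analysis.
2. In the imaging outcomes section, replace the conditional wording on mixed models with a commitment to use them for this fNIRS outcome. The argument here does not extend to functional connectivity, for which Table 1 lists two scans.
3. Reconcile Table 1 with the fNIRS acquisition section and the Discussion on the number of fNIRS recordings.

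The cost is wording. No new data are needed and standard software fits the model. The one small burden is that the covariance structure must be fixed in advance.

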### Sample size

This study employes a three-arm, parallel-group, randomized controlled design (1:1:1 allocation), with the MoCA score as the primary endpoint. One-way analysis of variance (ANOVA) is used to compare differences among the three groups. Due to the lack of a clear anticipated effect size, based on previous rTMS studies in PSCI (26–28), we adopt Cohen’s f ≈ 0.32 as the expected effect size. Using G*Power 3.1 (test type: one-way ANOVA; effect size *f* = 0.32; *α* = 0.05, two-tailed; power = 0.80), the estimated total sample size is 99 (33 per group) to detect significant differences in MoCA scores. To account for a potential 10% attrition rate, the final recruitment target is set at 105 participants (35 per group). Because *a priori* information on within-subject correlation and covariate R^2^ was unavailable, we used one-way ANOVA for conservative planning. The primary analysis will use longitudinal models with covariate adjustment, which is expected to provide equal or greater efficiency than the planning model.

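### The confirmatory fNIRS outcome is tested without pre-treatment activation as a covariate, a loss of precision (not validity) that a baseline-adjusted end-of-course comparison would recover at almost no cost

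*Protocol article*

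**What the plan says.** All places are in the Protocol article.

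- **Status of the outcome.** Primary and exploratory imaging outcomes names two primary imaging measures, one of them prefrontal activation during the verbal fluency task by fNIRS: "These primary endpoints are considered confirmatory, with hypothesis testing guided by FDR correction as described below".
- **Recordings.** fNIRS data acquisition gives "three time points (before the first treatment, after the first treatment, and after the last treatment"). Table 1 marks fNIRS at baseline and week 3 only. A pre-treatment recording exists on either reading.
- **Tests.** fNIRS data processing and analysis lists comparisons, "including between-group and within-time point comparisons using ANOVA or nonparametric tests as appropriate", and then "Repeated measures analysis of variance will be used to test Group × Time interaction effects". It does not say which of the two carries the confirmatory label.
- **Adjustment elsewhere.** The regression in Clinical data analysis is for MoCA change and key secondary cognitive outcomes. Its covariates are age, sex, education, time since stroke, rehabilitation dose and lesion side, with no baseline value of any outcome. The same model is extended to key imaging outcomes only for an exploratory Group × Lesion Side term. The imaging section says mixed models will be considered where feasible, to limit bias from missing data.

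**The concern.** A recording taken before treatment predicts later recordings of the same region to some degree. Used as a covariate, it removes the predictable part of the between-patient variance from the group comparison. The two planned tests handle it less efficiently, in opposite ways:

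- The time-point comparison leaves it out, and so loses most when the correlation is high.
- The Group × Time test subtracts it in full. With two recordings the interaction is the same test as an unadjusted comparison of change scores. With three it is a 4-df test. It loses most when the correlation is low.

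The Sample size section says that within-subject correlation was not available, so the sponsor cannot know which case applies. At stake is power on an outcome called confirmatory, with at most 35 patients per arm. The Discussion also concedes that active rTMS in every arm may narrow between-group differences.

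**Working it through.** **Inputs**

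- Effect size: "f ≈ 0.32 as the expected effect size" (Sample size). It is stated for MoCA and borrowed here, because none is given for fNIRS.
- Error rate: "0.05, two-tailed; power = 0.80" (Sample size). The figures below are for one test at 0.05, without the planned FDR step.
- Imaging sample: 105 recruited, less about 10% imaging attrition: 105 × 0.9 = 94.5, taken as N = 94.
- Correlation rho between recordings: not given. Assumed 0.5, range 0.3 to 0.8, equal between all recordings, with equal variances.

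**The plan's own figure.** For a one-way ANOVA with three groups, the noncentral F with lambda = N f² and df 2, N − 3 gives a minimum N of 98, or 99 with equal groups, and power 0.808 at 99. This reproduces "the estimated total sample size is 99 (33 per group").

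**Four tests of the group effect, N f² = 94 × 0.1024 = 9.63**

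1. Time-point ANOVA on the last recording: lambda = N f², df 2, N − 3.
2. Group × Time, two recordings (change score): lambda = N f² / [2(1 − rho)], df 2, N − 3.
3. Group × Time, three recordings: lambda = N f² × (2/3) / (1 − rho), df 4, 2(N − 3). The factor 2/3 is the sum of squares of the centred effect profile when the effect is at the last recording only. It is also 2/3 when the effect is equal at both post-treatment recordings.
4. ANCOVA on the last recording: lambda = N f² / (1 − rho²), df 2, N − 4.

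At rho = 0.5 the lambdas are 9.63, 9.63, 6.42/0.5 = 12.83 and 9.63/0.75 = 12.83. Tests 3 and 4 then have the same lambda, and the difference in power comes almost entirely from spending 4 df rather than 2.

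| rho | Time-point ANOVA | G × T, two recordings | G × T, three recordings | ANCOVA | Gain in points over each |
|---|---|---|---|---|---|
| 0.3 | 0.786 | 0.632 | 0.660 | 0.825 | 3.9 / 19.3 / 16.5 |
| 0.5 | 0.786 | 0.786 | 0.821 | 0.894 | 10.8 / 10.8 / 7.3 |
| 0.6 | 0.786 | 0.873 | 0.905 | 0.937 | 15.1 / 6.4 / 3.2 |
| 0.7 | 0.786 | 0.951 | 0.970 | 0.976 | 19.1 / 2.5 / 0.6 |
| 0.8 | 0.786 | 0.994 | 0.998 | 0.997 | 21.1 / 0.3 / −0.1 |

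**Checks**

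- A 4,000-run simulation at N = 99 and rho = 0.5, with equal effect at both post-treatment recordings, gave 0.811, 0.809, 0.849 and 0.909. The formulas give 0.808, 0.808, 0.843 and 0.910.
- Effect size, at rho = 0.5 and N = 94: with f = 0.25 the gains are 13.3, 13.3 and 11.1 points; with f = 0.40 they are 4.5, 4.5 and 2.3.
- Effect profile: if the effect after the first session is half the final effect, the three-recording test has power 0.684 at rho = 0.5 and f = 0.32, so ANCOVA gains 21 points. If the effect is present only after the first session, the three-recording test has power 0.82, and last-recording ANCOVA has only its 5% error rate.
- Sample size at rho = 0.5 and f = 0.32: ANCOVA needs 74 patients for 80% power, against 98 for the plain ANOVA.

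**The case against.** The best argument against the point is about the question asked. The Discussion says fNIRS is recorded three times to separate an immediate response from a lasting one. That is a question about the time profile, and Group × Time over three recordings tests it directly. Last-recording ANCOVA tests something narrower and, as shown above, misses an effect confined to the first session. A reader might infer that ANCOVA answers the stated fNIRS question and should replace the interaction. The documents do not support that, and Group × Time should stay for this aim.

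A reader might also infer that the planned tests are biased or inflate false positives. They do not: under randomization each holds its error rate, and chance baseline imbalance is part of the sampling variance that the tests already count.

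Third, the figures rest on a MoCA effect size and an assumed correlation, and they leave out the FDR step. That stands, and for that reason only a range is offered.

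Fourth, the trial's primary outcome is MoCA, the Limitations section calls the trial exploratory, and detail is often left to an SAP. This bears on priority but does not dispose of the point. The article names the tests for an outcome it calls confirmatory, so the point concerns a stated choice. The lesion-side model and the possible mixed models do bring some adjustment to imaging, but neither commits to a baseline covariate.

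**Conclusion.** The point holds as one of precision. The confirmatory fNIRS tests leave usable baseline information aside, and no other section restores it. Under f = 0.32, N = 94 and a single test at 0.05, baseline adjustment of the last recording gains about 4 to 19 points over the time-point ANOVA as rho rises from 0.3 to 0.7. The gain over Group × Time falls from about 19 points to 1 across the same range, with the effect at the last recording only, and is essentially zero at 0.8. The 7 to 11 points at rho = 0.5 illustrate one assumed case and are not a property of this plan. The comparison with the three-recording interaction is also between tests of different hypotheses. What favours ANCOVA for the end-of-course comparison is that it is best, or within 0.2 points of best, at every correlation examined, when the correlation is unknown. The change is worth making before the data are analysed, but the trial does not stand or fall on it.

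**What to change.** In fNIRS data processing and analysis, state that the confirmatory end-of-course between-group comparison is an ANCOVA of prefrontal activation after the last treatment on group, with pre-treatment activation of the same region as covariate. Lesion side, already recorded, may be added. Report baseline-adjusted differences with 95% confidence intervals.

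Keep Group × Time as the test of acute versus cumulative change. If activation after the first session is also compared with baseline adjustment, either label that analysis secondary or include it in the FDR family, so that the extra test is accounted for.

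The cost is one or two sentences, no new data, one degree of freedom per covariate, and a confirmatory test focused on the last recording.
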